#### Secondary Outcome Measures

The secondary outcome measures will be collected at baseline and immediately after the treatment for all participants. We designed DigiCOVID to improve mental well-being. Therefore, we will measure the impact of the intervention by looking at pre-post changes in the following outcome measures: the 12-item General Health Questionnaire [26] , the Impact of Event Scale–Revised [27], the 7-item General Anxiety Disorder scale [28], the Insomnia Severity Index [29], and the 9-item Patient Health Questionnaire [30]. We expected to observe a significant improvement across all these secondary outcome measures *P*< in both patients with COVID-19 and their family members. To verify these experimental hypotheses, we will conduct the analysis based on the preintervention (baseline) and postintervention data, using parametric and nonparametric statistical tests. The criterion for statistical significance is *P*<.05. Results with *P*<.1 will be described as trends.

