### Data Analysis

There are 3 a priori defined analysis populations, including a primary analysis population, a secondary analysis population designed to compare effect sizes in populations with no missing data, and a population who completed all study visits. The 3 populations are as follows:

ITT population: this is the a priori primary analysis population, defined as including all participants who attended at least 4 remote psychotherapy sessions.Intention-to-treat fully evaluable (ITT-FE) population: this is a secondary analysis population, defined as including all members of the ITT population who complete a postintervention visit. Note that a participant may complete a specific visit but have missing data for a test, in which case the participant is in the overall ITT-FE population but does not contribute data to the ITT-FE population for that visit (eg, the number of evaluable cases for a specific test on a specific visit may be smaller than the ITT-FE population for that visit because of missing data).Intention-to-treat completers (ITT-C) population: this is a secondary analysis population, defined as including all members of the ITT-FE population who complete all intervention sessions. Note that the ITT-C population is a strict subset of the ITT-FE population; a person who completes the treatment but does not complete the postintervention evaluation visit is not a member of the ITT-C population.

We also plan to perform different analyses in order to better describe the demographics of patients and relatives and to test whether there are significant differences in terms of response to our psychotherapy intervention.

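### A written rule labels P<.1 a trend on top of an unadjusted P<.05 across ten secondary pre-post tests, in a study that intends to speak about efficacy

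*Protocol article*

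**What the plan says.** The Secondary Outcome Measures section of the protocol article lists five self-report scales: general health (12 items), impact of events, anxiety (7 items), insomnia and depression (9 items). All are measured at baseline and just after treatment. The stated hypothesis is "We expected to observe a significant improvement across all these secondary outcome measures", and it applies "in both patients with COVID-19 and their family members".

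The analysis is to be done "using parametric and nonparametric statistical tests"; the section does not say which type applies when. Two thresholds follow. The first is "The criterion for statistical significance is *P*<.05". The second is "Results with *P*<.1 will be described as trends". No scale is named as the leading one, and no adjustment for several tests is mentioned.

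The Data Analysis section adds "There are 3 a priori defined analysis populations" and ranks them: "ITT population: this is the a priori primary analysis population", with the fully evaluable and completer populations as secondary. It also announces comparisons of response between patients and relatives, without giving their number.

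**The concern.** Five scales in two groups give ten chances to meet an unadjusted criterion. The trend rule then gives directional wording to results that miss the article's own criterion. Nothing in the text prevents one or two such results from being picked out as the signal.

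The secondary label does not make this harmless. The abstract's conclusions name preliminary efficacy as an aim. The Expected Outcomes section expects the programme to work in both groups and looks ahead to analyses that will settle efficacy and effectiveness. By the article's own account (Overall Design and Timeline), relatives were added to a design registered for patients only. That takes the family from five tests to ten, and the article states the same criterion for both groups.

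**Working it through.** The article states no familywise error rate, so there is no figure of its own to reproduce. The check asks how often at least one false finding would appear if no scale truly changed.

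**Inputs from the article**
- Scales: 5. Groups: 2. Tests: 5 × 2 = 10, counting one test type and one population.
- Thresholds: 0.05 for significance and 0.10 for a trend, so the trend rule doubles the per-test threshold (0.10 / 0.05 = 2).

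**Assumptions, not in the article**
- Tests are two-sided; sidedness is not stated. A false improvement then has half the two-sided rate: 0.025 at P<.05 and 0.05 at P<.1.
- The two groups are independent.
- Change scores on the five scales within a group correlate 0, 0.3, 0.5 or 0.7.
- In the simulation, each group has 40 participants.

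**Independent tests:** chance of at least one = 1 − (1 − α)^10
- Either direction, P<.05: 1 − 0.95^10 = 40.1%
- Either direction, P<.1: 1 − 0.90^10 = 65.1%
- Improvement only, P<.05: 1 − 0.975^10 = 22.4%
- Improvement only, P<.1: 1 − 0.95^10 = 40.1%

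**Correlated scales:** simulation under no change, 3,000 runs, paired t test, same ten tests

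| Correlation | Any, P<.05 | Any, P<.1 | Improvement, P<.05 | Improvement, P<.1 |
|---|---|---|---|---|
| 0.3 | 36.0% | 60.7% | 19.0% | 34.9% |
| 0.5 | 33.3% | 55.2% | 18.6% | 31.9% |
| 0.7 | 27.7% | 47.0% | 15.0% | 25.9% |

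**If every look is taken.** The simulation was extended so that both a t test and a Wilcoxon signed-rank test are run on each scale, in the full group and in a completer subset of 80% (assumed). The ITT and fully evaluable populations coincide for complete pre-post pairs, so they count once. For correlations 0.3 to 0.7, improvement-only error is 31% to 23% at P<.05 and 50% to 38% at P<.1. It reaches 58% at P<.1 only if the scales are uncorrelated.

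**Checking the remedy.** A per-test level of 0.05 / 10 = 0.005 gives 1 − 0.995^10 = 4.9% over ten independent tests. Holm starts from that same level and controls the familywise rate at 5%. Holm applied separately within each group of five allows up to 1 − 0.95^2 = 9.75% across both groups.

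**The case against.** Several objections have weight.

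- **A reader might infer that a false improvement is likely.** The figures do not support that. The 40% and 65% include false worsenings. Counting improvements alone, the ten tests stay at or below about 40% even with trends included. The chance passes 50% only if nearly uncorrelated scales, trends and every possible look are combined.
- **A reader might multiply 5 scales × 2 groups × 3 populations × 2 test types into 60 chances.** Sixty is at most a ceiling on the number of P values. The populations are nested and ranked, with ITT declared primary. Naming both test types may mean choosing one according to the distribution; the text does not say both are run on every scale.
- **The hypothesis is of improvement on all scales.** If success required every scale, error would not inflate. But the text states this as an expectation, not as a decision rule.
- **These are secondary outcomes of a feasibility study.** Statisticians differ on whether such outcomes need formal adjustment, and an adjustment or a test-choice rule may sit in a full protocol or SAP that is not shown. Their absence from the article is therefore not the finding.
- **The trend label is declared in advance and kept apart from significance.** That is true, and it is more open than adding the label later. It still permits a directional statement at twice the stated threshold.

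The two written rules remain. A fuller document could add a multiplicity procedure, but the trend sentence would still stand in the published plan and would sit badly with it.

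**Conclusion.** The point holds in a limited form. The article fixes an unadjusted P<.05 for ten secondary pre-post tests and a P<.1 trend label on top. With no true change, at least one false improvement would appear in about 15-22% of such studies at P<.05 and in 26-40% once trends count. For a finding in either direction the figures are 28-40% and 47-65%. The lower ends assume a correlation of 0.7 between scales and the upper ends assume independence. All figures assume two-sided tests and independent groups. If the tests were one-sided towards improvement, the independent-case figures for a false improvement would be 40.1% and 65.1%.

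This is well above a nominal 5%, but it does not make a false improvement probable. It concerns how secondary results are described, not the primary feasibility outcomes. The trend sentence is the clearest defect because it is an explicit rule; the unadjusted ten tests are the setting that gives it weight.

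**What to change.** 1. Delete the sentence on trends.
2. Report every scale in each group as mean change with 95% CI in the ITT population, which the article already declares primary.
3. Name one prespecified test per scale as the inferential one and keep the other type as a sensitivity analysis only.
4. Either describe the secondary results as exploratory and unadjusted over ten tests or, if significance claims are kept, apply Holm across all ten. If Holm is applied within each group instead, state that about 10% overall is accepted.

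The change needs a few sentences and no new data. Its cost is that somewhat fewer results will be called positive. The Results section says preliminary analyses are already complete, so the change should be declared as made after them and not presented as part of the original plan.

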### Data Collection

The sources of the research material will consist of data collected through assessment visits and the DigiCOVID app, strictly for research purposes. Participants will be carefully screened for contraindications prior to participation. All intervention data are coded so as not to identify any given participant and be securely stored. Hard copy data from the neuropsychological tests will be stored in a locked file cabinet in a safe location with limited access by authorized personnel or on password-protected computers in locked offices. All data from this trial will be recorded on a secure, web-based software application designed to support data capture for research studies. To achieve robust and unbiased results, data will undergo a rigorous quality control process to ensure consistency in scoring, coding, and accuracy of data entry. Standard data quality procedures will be used, including double scoring, random spot checking of assessments, and electronic data capture. Additionally, 20% of all data folders will undergo a random audit every 3 months. The database will be designed to not allow illegal values in entry. Any outliers will be double-checked with the raw data for accuracy.

### Data Analysis

There are 3 a priori defined analysis populations, including a primary analysis population, a secondary analysis population designed to compare effect sizes in populations with no missing data, and a population who completed all study visits. The 3 populations are as follows:

ITT population: this is the a priori primary analysis population, defined as including all participants who attended at least 4 remote psychotherapy sessions.Intention-to-treat fully evaluable (ITT-FE) population: this is a secondary analysis population, defined as including all members of the ITT population who complete a postintervention visit. Note that a participant may complete a specific visit but have missing data for a test, in which case the participant is in the overall ITT-FE population but does not contribute data to the ITT-FE population for that visit (eg, the number of evaluable cases for a specific test on a specific visit may be smaller than the ITT-FE population for that visit because of missing data).Intention-to-treat completers (ITT-C) population: this is a secondary analysis population, defined as including all members of the ITT-FE population who complete all intervention sessions. Note that the ITT-C population is a strict subset of the ITT-FE population; a person who completes the treatment but does not complete the postintervention evaluation visit is not a member of the ITT-C population.

We also plan to perform different analyses in order to better describe the demographics of patients and relatives and to test whether there are significant differences in terms of response to our psychotherapy intervention.

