## Methods

### Overall Design and Timeline

The study is conducted jointly by the units of pneumology, internal medicine, psychiatry, and the laboratory of brain injury and therapeutic strategies of the Istituto di Ricerche Farmacologiche Mario Negri. Before accessing DigiCOVID, participants are taken through the following steps: first, participants undergo an initial screening to ensure the main inclusion criteria are met. Then, 2 trained neuropsychologists remotely perform neuropsychological tests on patients via Zoom. The tests are aimed at assessing patients’ IQ through the Test di Intelligenza Breve (Italian for brief intelligence test) [23] and standard progressive Raven matrices [24]. Suicidality is assessed via the Columbia Suicide Severity Rating Scale [25]. Finally, participants complete a battery of web-based self-reports that include the following: the 12-item General Health Questionnaire [26], the Impact of Event Scale–Revised [27], the 7-item General Anxiety Disorder assessment [28], the Insomnia Severity Index [29], and the 9-item Patient Health Questionnaire [30]. After completing these assessments, participants are assigned to a trained psychotherapist who offers 8 teletherapy sessions carried out through Zoom.

This model is designed to be applied to patients with COVID-19 during hospitalization, after discharge, as well as during the remission and recovery phases. Similarly, this model is intended to be delivered to people who are dealing with the hospitalization or discharge after COVID-19 of a family member or have lost a family member due to COVID-19. A total of 8 remote, 50-minute, individual psychological sessions are offered weekly using secure videoconferencing software. The severity of the clinical conditions of patients with COVID-19 has largely influenced the sequencing of the intervention.

During all phases of the clinical work, suffering is contextualized both in the light of the recent traumatic experience (eg, bereavement, hospitalization in intensive care, and fear for one’s life or that of a relative) and in the light of historical ways of suffering, so that the patient is able to recognize the meaning of the symptoms experienced.

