#### Recruitment

As of April 2022, 122 participants have been referred to the study. Participation is voluntary, and an extended informed consent form is signed before any evaluation, assessment, or voice and video call. Consent forms are collected remotely for those who have been discharged and are currently in remission and in person for those hospitalized in a COVID-19 ward of either pneumology, internal medicine, or infectious disease departments.

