### Primary and Secondary Outcome Measures

#### Primary Outcome Measures

Efforts will be made to assess all participants who have completed the minimum required intervention activities. For DigiCOVID, the minimum required intervention activities include attending psychotherapy sessions at least 4 times. As the main goal of this project is to evaluate the feasibility, acceptability, and usability of DigiCOVID, we will conduct an analysis of the following primary outcome measures in all intention-to-treat (ITT) participants:

Assessment completion rate—based on our previous studies, we expect ≥80% of participants will complete the battery of web-based self-reports.Usability ratings obtained post DigiCOVID via a 7-point Likert scale questionnaire (ie, mean rating of all responses)—this is a brief and embedded poststudy questionnaire on program satisfaction, clarity, and perceived benefits. Participants will rate each sentence on the following 7-point Likert scale: 1=completely agree; 2=mostly agree; 3=somewhat agree; 4=undecided; 5=somewhat disagree; 6=mostly disagree; and 7=completely disagree. Based on our previous studies, we hypothesize exit survey ratings of at least ≥4.5 (SD 1.5) on the 7-point Likert scale items.Reported side effects (ie, raw score)—based on our previous findings, we expect 0 adverse events due to program use.Overall program completion rate—based on previous findings, we hypothesize full program completion in ≥70% study participants.

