## Results

This project has been funded by Fondazione Cariplo under Award number 2020-1366, in June 2020. As of April 2022, we enrolled a total of 122 subjects, of which 94 have completed neuropsychological tests and web-based questionnaires; data analyses are currently completed in terms of preliminary results, and we expect results to be published by the end of 2022.

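### The primary ITT population is a minimum-exposure set (at least 4 of 8 sessions), so participants who leave before session 4 are missing from the feasibility and side-effect results

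*Protocol article*

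**What the plan says.** The Data Analysis section of the protocol article names three populations. The first is primary: "ITT population: this is the a priori primary analysis population, defined as including all participants who attended at least 4 remote psychotherapy sessions". The second is the part of that set with a postintervention visit. The third is the part of the second that finished every session. Each is nested in the one before.

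Under Primary Outcome Measures the article states: "we will conduct an analysis of the following primary outcome measures in all intention-to-treat (ITT) participants". The outcomes are assessment completion (at least 80%), usability ratings, side effects and program completion. For the last two it says "we expect 0 adverse events due to program use" and "we hypothesize full program completion in ≥70% study participants". The same section directs assessment efforts to participants who reached the 4-session minimum, whereas Secondary Outcome Measures speaks of collecting data on all participants.

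Overall Design and Timeline sets the program at 8 weekly sessions and puts the baseline assessments first: "After completing these assessments, participants are assigned to a trained psychotherapist who offers 8 teletherapy sessions". The self-report battery is repeated at the end of the cycle.

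**The concern.** Feasibility, acceptability and usability are the main goal of the study. Whether people keep attending is therefore the result being sought, yet attendance also decides who enters the primary analysis. A participant for whom the remote format fails in the first three sessions is removed before the completion rate is calculated. One who stops early because of an adverse effect is not in the set in which side effects are counted. The Limitations section reports low motivation in some patients and links it to the remote format, so early loss is a realistic prospect here.

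The label adds to the problem. Readers take intention-to-treat to mean that nobody was removed for what happened after entry, and the completion target is worded as a share of study participants. Because the other two populations are subsets, no planned analysis would reveal the difference.

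**Working it through.** The article gives no expected number reaching session 4, so there is no figure of its own to reproduce. The check is on denominators.

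**Inputs**
- Program length 8 sessions (Overall Design and Timeline); entry to the primary set at 4 or more (Data Analysis).
- Targets 70%, 80% and 0 events (Primary Outcome Measures).
- N = 122. Recruitment says "As of April 2022, 122 participants have been referred to the study"; Results says "we enrolled a total of 122 subjects, of which 94 have completed neuropsychological tests and web-based questionnaires". Whether 122 counts people referred or enrolled is unresolved, so it serves only as an illustrative total.
- q, the share of the 122 who reach session 4: not given. Assumed range 60% to 90%.

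**Program completion.** A completer has attended all 8 sessions and so is always in the 4-session set. With C completers and n4 people reaching session 4, the planned rate is C/n4 and the full rate is C/N. Since n4 = qN, planned rate = full rate / q. The planned rate is higher whenever q is below 1 and C is above 0.

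Fewest completers that meet 70% of n4, as a share of all 122 (n4 = 122q rounded; C = 0.70 × n4 rounded up):

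| q | n4 | C | C/122 |
|---|---|---|---|
| 100% | 122 | 86 | 70.5% |
| 90% | 110 | 77 | 63.1% |
| 80% | 98 | 69 | 56.6% |
| 77% | 94 | 66 | 54.1% |
| 60% | 73 | 52 | 42.6% |

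The 77% row corresponds to all 94 assessed participants reaching session 4. If the baseline assessments must come first, that is the ceiling on the April 2022 counts.

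In the other direction, suppose true completion among all 122 is 55% (assumed). The planned analysis would show 0.55/0.90 = 61%, 0.55/0.80 = 69%, 0.55/(94/122) = 71%, or 0.55/0.70 = 79%.

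**Side effects.** Events in people who stop before session 4 are not counted, so the count can only be equal to or lower than the count among all starters. Zero events also supports less in a smaller set. The one-sided 95% upper bound, 1 − 0.05^(1/n), is 2.4% for n = 122, 3.1% for n = 94 and 4.0% for n = 73, and it says nothing about those excluded.

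**Assessment completion.** The article does not say which battery the 80% refers to.
- Baseline: the battery precedes therapist assignment, so everyone with 4 sessions has done it. The rate is 100% by construction.
- Post-treatment: the rate is not fixed in advance, but early leavers are omitted. It is overstated if they complete the battery less often than those who stay, which is likely but is not arithmetic.

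**Usability** ratings come after the program and carry the same restriction.

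**The case against.** The rule is disclosed, was set a priori, and matches the stated minimum exposure. A minimum-exposure set is a legitimate secondary population. People who stop after session 4 stay in the denominator, so only early dropouts are lost. All of this stands, but it does not make the set a sound denominator for completion or harms.

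Several stronger readings are tempting, and the documents do not support them.
- *Assessment completion already misses its target, since 94/122 = 77%.* The 94 finished neuropsychological tests as well as questionnaires, while the target concerns questionnaires only. The count is interim, as recruitment was still being completed. Some of the other 28 may be pending, or ineligible on criteria assessed before therapy, such as IQ. The figure should not be compared with 80%.
- *The program could pass with under half of starters finishing.* The number of starters is not given. With a constant dropout set so that exactly 70% go from session 4 to session 8, session 1 to session 8 has seven transitions and gives 0.70^(7/4) = 54% of starters. A figure of 0.70² = 49% applies to everyone assigned, including people who never attend. Both rest on an assumed dropout pattern.
- *Baseline completion is certain to be 100%.* This holds only on the baseline reading. The paragraph's opening, on assessing those who reached the minimum, points rather to the post-treatment battery.

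Two cautions also bear on the remedy. Post-treatment data on early leavers may not exist, because assessment efforts are promised only for those with 4 sessions. The targets come from previous studies whose denominators are not shown, so moving them to a wider set needs justification.

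**Conclusion.** The primary population is wrongly labelled and is the wrong denominator for this trial's main outcomes. That conclusion rests on the stated definitions alone. For program completion the direction is certain once anyone leaves before session 4: the planned rate exceeds the rate among all participants. The side-effect count can only stay equal or fall. For assessment completion the effect depends on which battery is meant.

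The size is not known. Under the assumed 60% to 90% reaching session 4, between 43% and 63% of all 122 completing would satisfy a target worded as 70% of study participants. That range depends on q and on taking 122 as the full total. It does not show that the program is infeasible or unsafe. It shows that the planned analysis could not tell.

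**What to change.** - **Program completion:** make the primary denominator everyone assigned to a therapist, with non-starters and dropouts counted as not completed.
- **Side effects:** count them in everyone who attended at least one session.
- **Assessment completion:** state which battery the 80% refers to. Report baseline completion in all consented, eligible participants and post-treatment completion in all assigned. State how many were never approached, so that they are not mistaken for refusals.
- **Label:** rename the 4-or-more-session set 'minimum exposure' and keep it as a secondary set.
- **Benchmarks:** state whether the 70% and 80% targets were derived on a comparable denominator.
- **Flow:** say whether 122 is referred or enrolled, and how the 28 without complete assessments divide into ineligible, pending and not completed.
- **Disclosure:** record the change as made after preliminary analyses, which Results says are complete.

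The cost is a revised population section, attendance and side-effect data on early leavers (whose availability the sponsor must confirm), probably less favourable feasibility rates, and a disclosed late change to the primary set.
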